### Outcomes {12}

The primary endpoint will be the percentage of gross total resection. The secondary endpoints will include facial nerve function, hearing preservation, surgical position placement time, time of operation (skin-to-skin surgical time), hospital stay, total hospitalization fee, and complications. The details of the primary and secondary outcomes are provided in Table 3.

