#### Sample size {14}

The sample size was calculated from the primary endpoint. We calculated the sample size as of September 2019 based on the results of the only multicentre randomized controlled trial in which the percentage of gross total resection in the SSP and LP were 93% and 73%, respectively [14]. The sample size calculated by PASS version 15 is 58 participants per group (overall sample = 116 participants) according to the above data with a power of 80%, an alpha risk of 5%, and an estimated shedding rate of 8%.

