### Assignment of interventions: allocation

#### Sequence generation {16a}, concealment mechanism {16b}, and implementation {16c}

Randomized lists will be created before the beginning of the study by SPSS version 21. Then, several sealed and opaque envelopes will be made and kept securely by recognized third parties. To ensure the balance of the number of patients and age distribution between the two groups, we considered age stratification (18–35 years old and 36–65 years old) with an appropriate block size. After the patient is enrolled, the sealed envelope system will be used for the randomization of the patients into two groups. Neither the investigator nor the participants will be aware of each envelope’s contents.

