## Statistical methods

### Statistical methods for primary and secondary outcomes {20a}

All analyses will be performed using the SPSS software, version 25 (IBM Corp.) with a two-sided significance level of .05 unless otherwise stated. Continuous quantitative variables are expressed as numbers, means, standard deviations, and medians. Comparisons between proportions for the categorical variables will be performed using the chi-square test, Fisher’s exact test, or Mann-Whitney *U* test. In addition, Student’s *t* test and non-parametric analysis will be used for continuous variables with and without normal distributions. Differences in the percentage of gross total resection, facial nerve function, hearing function, general complications, and special complications between the SSP and LP groups will be evaluated using Fisher’s exact test or chi-squared test. Differences in the surgical positioning time, time of operation, hospital stay, and total hospitalization fee between the SSP and LP groups will be evaluated using Student’s *t* test or Mann-Whitney *U* test. Regression analysis will be used to evaluate the influence of SSP versus LP, tumour size, and surgeons on the percentage of gross total resection, as well as SSP versus LP, tumour size, surgeons, and the percentage of gross total resection on facial nerve function and hearing function. Association of the time of operation with SSP versus LP, tumour size, the percentage of gross total resection, and surgeons will be evaluated using ANOVA. If the patient has a PFO, he or she will not be excluded from the study but analysed according to the SSP group they were originally assigned after the LP surgery.

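### The listed analyses leave out the age stratum used at randomisation, and the primary test is not fixed between Fisher and chi-squared, which differ in power at the planned size (minor).

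*Protocol article*

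**What the plan says.** All references are to the protocol article.

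- **Outcomes {12}:** "The primary endpoint will be the percentage of gross total resection". For each patient this is a yes/no outcome.
- **Sequence generation {16a}:** "To ensure the balance of the number of patients and age distribution between the two groups, we considered age stratification", with strata 18–35 and 36–65 and blocking. No other stratification factor is named.
- **Sample size {14}:** the design rates are given as "the percentage of gross total resection in the SSP and LP were 93% and 73%, respectively", "with a power of 80%, an alpha risk of 5%, and an estimated shedding rate of 8" per cent. The result is 58 per group, 116 in all. The test behind the calculation is not named.
- **Statistical methods {20a}:** testing is done "with a two-sided significance level of .05 unless otherwise stated". Gross total resection, along with four other categorical outcomes, is compared between positions by either the Fisher or the chi-squared test. Neither a selection rule nor a position on continuity correction is given. Separately, "Regression analysis will be used to evaluate the influence of SSP versus LP, tumour size, and surgeons on the percentage of gross total resection". The regressions for facial nerve and hearing function add resection to those three terms, and so does the ANOVA for operation time. Age is in none of these lists. Elsewhere it appears only as an eligibility limit and a baseline variable.

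**The concern.** Two things do not fit together.

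First, the only factor used to balance the arms is missing from analyses whose terms are spelled out. Stratified allocation makes the arms more alike on age than simple randomisation would. If age predicts resection, a test that ignores the stratum uses a slightly too large variance. It is then somewhat conservative and gives up a little precision.

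Second, the primary comparison is left as a choice between tests that do not behave alike at this sample size. The success rates are high and the arms are small, so Fisher and the continuity-corrected chi-squared are noticeably more conservative than the uncorrected test. A result near the 5% boundary could be called positive or negative depending on a choice the text leaves open.

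**Working it through.** **Inputs.** Rates 0.93 and 0.73, two-sided alpha 0.05, power 80%, loss 8%, 58 per arm (Sample size {14}; sidedness from Statistical methods {20a}). Evaluable per arm: 58 × 0.92 = 53.4, taken as 53.

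**Step 1: reproduce the plan's 58.** The pooled rate is 0.83; 0.93×0.07 + 0.73×0.27 = 0.2622; the difference is 0.20.

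- Pooled, uncorrected: n = [1.960·√(2×0.83×0.17) + 0.842·√0.2622]² / 0.20² = 54.2, so 55. Then 55/0.92 = 59.8, so 60.
- Unpooled, uncorrected: n = (1.960 + 0.842)² × 0.2622 / 0.20² = 51.4, so 52. Then 52/0.92 = 56.5, so 57.
- Two-sided with continuity correction: n = (54.2/4)·[1 + √(1 + 4/(54.2×0.20))]² = 63.8, so 64. Then 64/0.92 = 69.6, so 70.

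The planned 58 lies between the two uncorrected results (57 and 60) and well below the corrected one. A one-sided corrected calculation gives 53, then 58 after loss, an exact match, but the plan states two-sided testing.

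**Step 2: exact power by test.** For each pair of success counts (i, j), the two binomial probabilities are multiplied, and the products are summed over the pairs each test declares significant.

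| Evaluable per arm | Uncorrected chi-squared | Fisher | Corrected chi-squared |
|---|---|---|---|
| 53 | 81.1% | 73.6% | 72.5% |
| 58 (no loss) | about 85% | 77.7% | 77.6% |
| 61 | 86.1% | 80.3% | 80.3% |

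Fisher first reaches 80% at 61 evaluable per arm, which is 61/0.92 = 66.3, so 67 per arm or 134 in total.

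At 53 per arm, Fisher and the uncorrected chi-squared disagree in 7.6% of trials at the design rates. In every such case the chi-squared is significant and Fisher is not. With 83% in both arms, the type I error is 4.9% for chi-squared and 2.8% for Fisher.

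**Step 3: how often would Fisher be used?** Suppose Fisher is used only when an expected count is below 5 (a customary rule, not one the article states). Expected failures per arm are 0.17 × 53 = 9.0. The rule is triggered when fewer than 10 failures occur in total, which has probability 0.8%. Overall power under the rule is 81.1%.

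**Step 4: what the age stratum is worth.** The documents give neither the age split nor an age effect. Assumed: 16 younger and 37 older patients per arm (30% younger), and the same odds ratio for resection, younger versus older, in both arms. The marginal rates are held at 93% and 73%, because those are the rates the trial was sized on. Power and type I error (83% in both arms) come from enumerating the four binomials.

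| Assumed age odds ratio | Power, chi-squared | Power, Cochran-Mantel-Haenszel | Type I error, chi-squared | Type I error, Cochran-Mantel-Haenszel |
|---|---|---|---|---|
| 1 | 81.1% | 81.2% | 4.9% | 5.0% |
| 1.5 | 81.2% | 81.3% | 4.9% | 4.9% |
| 2 | 81.3% | 81.6% | 4.8% | 4.9% |
| 3 | 81.4% | 82.0% | 4.7% | 4.9% |
| 4.5 | 81.6% | 82.6% | 4.5% | 4.9% |

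Simulation at an odds ratio of 4.5 agrees to within its error (81.5% v 82.5% power; 4.6% v 5.0% type I error). If the effect ran the other way, with older patients 4.5 times as likely in odds to have total resection, the same enumeration gives 82.1% v 84.2%, a gain of about 2 points.

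**The case against.** Four points can fairly be made on the other side.

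- **The either/or is ordinary shorthand.** The sentence covers five categorical outcomes, some of which may be rare, and is commonly read as choosing by cell counts. On that reading Fisher almost never reaches the primary endpoint (Step 3). The customary rule also depends on pooled counts rather than on the difference between arms, so it is hard to exploit. This largely stands. What remains is that the rule is unwritten and that the chi-squared version is not specified.
- **The roles can be inferred.** Differences between groups go to the simple test, the regression is given the job of examining influences, and the sample size rests on two proportions. The unadjusted comparison is the natural primary analysis. This stands in part; an explicit label would settle it.
- **A condensed article may leave such detail to a fuller document.** This is reasonable for the selection rule. It excuses the age stratum less well, because the article lists its covariates term by term and omits the only stratification factor.
- **The stated purpose of stratifying is balance, and balance is achieved whatever the analysis.** This is true, and Step 4 shows that little precision is forgone.

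Two stronger readings are tempting and unsupported. A reader might infer that the trial is too small. It is not: the uncorrected chi-squared delivers the stated power. A reader might also infer that ignoring age makes the test invalid or costs much power. With the marginal rates held at the design values, chi-squared keeps at least 81% power in every scenario tried and errs on the conservative side.

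**Conclusion.** The point holds as a minor one. The design and the listed analyses do not match on age, and the primary test is left open between versions whose exact power at 53 per arm runs from 72.5% to 81.1%. The loss of about 7.6 points arises only if Fisher is used (8.6 for the corrected chi-squared). Under the customary expected-count rule that would happen for Fisher in under 1% of trials.

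The power figures by test rest on the article's own rates and loss. The size of the age effect rests on assumptions: a 30% younger share and odds ratios of 1.5 to 4.5 in favour of younger patients give 0.1 to 1 point of power, with the chi-squared type I error falling from 4.9% to about 4.5%. The gain is about 2 points if an equally strong effect runs the other way, and there is no loss if age has no effect. The documents do not allow a tighter estimate.

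**What to change.** In Statistical methods {20a}:

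1. Name one primary analysis of gross total resection that uses the randomisation age strata. One suitable choice is the Cochran-Mantel-Haenszel test without continuity correction, reported with a stratified risk difference and 95% confidence interval. A logistic model with position and age stratum would also serve; what matters is that one is named.
2. Label the regression on resection as supportive, and add the age stratum to position, tumour size and surgeon.
3. Keep Fisher's exact test for sparse outcomes such as complications, and state the rule that triggers it.

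The sample size need not change. If Fisher were kept for the primary endpoint, 80% power would need 67 per arm (134 in total).

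The cost is a change of wording. Age is already collected at baseline, no new data are needed, and nothing is lost if age proves unrelated to resection. Because the trial is already recruiting, the change should be dated and made before outcomes are compared by group.

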The goals of modern VS surgery are to completely remove the tumour, preserve nerve function, and reduce complications. In recent years, with the popularization and application of microscopy, continuous improvements in surgical instruments and skills, in-depth studies of the microanatomy of the cerebellopontine angle, and the application of intraoperative electrophysiological monitoring technology, the above surgical goals have largely been attained [12–15]. In addition, many factors affect the outcomes of surgery and related complications, among which the effect of different surgical positions has long been debated. Patients are easily placed in the lateral position (LP, Fig. 1B), and few complications are associated with this surgical position. However, corresponding disadvantages do exist, such as high cranial pressure, difficulty in releasing cerebrospinal fluid, unclear anatomical location, and increased requirements for assistants [5]. In contrast, the semi-sitting position (SSP, Fig. 1A) provides specific possible advantages, including drainage of blood and cerebrospinal fluid (CSF) by gravity, decreased bleeding, clean surgical field, improved surgical exposure and anatomical orientation, and ability to perform continuous bimanual dissection [5, 15–18]. However, this position carries some potential risks, such as venous air embolism (VAE) [19], tension pneumocephalus, and peripheral nerve injury [16, 20]. Despite these risks, some neurosurgeons preferred to perform posterior fossa surgeries in the SSP [15, 21]. Many studies have shown that the operational risk associated with body position is very low in the context of adequate preoperative preparation, intraoperative coordination with anaesthesiologists, and careful monitoring. Thus, SSP is safe and reliable [22–24]. [name] of Hannover, Germany, personally completed more than 4000 cases of semi-sitting VS resection. Long-term functional outcomes and surgery-related complication rates were satisfactory. Fifty patients with VSs > 4.0 cm in maximal extra-meatal diameter were reported with gross total resection, and the anatomical integrity of the facial nerve was preserved in 92% [25]. Taking all the above-mentioned advantages into consideration, SSP may lead to better surgical outcomes, such as a higher percentage of gross total resection and better facial nerve function, for patients with large VSs. However, randomized studies are required to verify this hypothesis.

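### The adjusted models for facial nerve function, hearing and operating time condition on gross total resection, a post-randomisation outcome, so their position term is not the randomised effect

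*Protocol article*

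**What the plan says.** Section {20a} of the protocol article contains two layers of analysis for the same secondary outcomes.

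- **Group comparisons.** Facial nerve function and hearing are compared between SSP and LP with a chi-squared or Fisher test, and operating time with a t test or Mann-Whitney test. None of these involves resection.
- **Multi-factor models.** For GTR itself: "Regression analysis will be used to evaluate the influence of SSP versus LP, tumour size, and surgeons on the percentage of gross total resection". For facial nerve function and hearing, the same sentence goes on "as well as SSP versus LP, tumour size, surgeons, and the percentage of gross total resection on facial nerve function and hearing function". For operating time: "Association of the time of operation with SSP versus LP, tumour size, the percentage of gross total resection, and surgeons will be evaluated using ANOVA".

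Elsewhere the protocol makes GTR an outcome that position should change. Outcomes {12}: "The primary endpoint will be the percentage of gross total resection". Sample size {14} rests on a previous trial in which "the percentage of gross total resection in the SSP and LP were 93% and 73%, respectively". The rationale {6a} expects that "SSP may lead to better surgical outcomes, such as a higher percentage of gross total resection and better facial nerve function".

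**The concern.** A variable that is fixed during the operation and that the allocated position is expected to alter is entered beside position as if it were a baseline covariate. This has two consequences.

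1. Any effect of position that runs through the extent of resection is removed from the position term. If SSP gave more complete resection at some cost to the facial nerve, that cost would be credited to resection and not to position.
2. Among patients with the same resection result, the two arms are no longer comparable. If GTR is easier to achieve in SSP, patients without GTR in that arm will tend to have the harder tumours. If the same difficulty also worsens nerve function, and the model does not capture it, the position term absorbs the difference. Tumour adherence is a possible example; it is my assumption and is not named in the protocol.

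The stated objective {7} is to compare the effects of the two positions on outcomes. A reader who takes the covariate-adjusted coefficient as the better answer to that question could be misled.

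**Working it through.** **Plan's own figure.** The 93% and 73% come from the sample size section. With two-sided 5%, 80% power and unpooled variance: n = (1.960 + 0.842)² × (0.93×0.07 + 0.73×0.27) / 0.20² = 7.85 × 0.2622 / 0.04 = 51.5, so 52 per group; 52/0.92 = 56.5, so 57. The pooled formula gives 55, and 55/0.92 = 59.8, so 60. The stated 58 lies between. It concerns GTR as an outcome only, so the present point does not touch it.

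**Which variables are in which model**

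| Outcome | Position | Tumour size | Surgeon | GTR |
|---|---|---|---|---|
| GTR (regression) | yes | yes | yes | is the outcome |
| Facial function, hearing (regression) | yes | yes | yes | yes |
| Operating time (ANOVA) | yes | yes | yes | yes |

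So one sentence treats GTR first as a result of position and then as a covariate next to position.

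**Size on the linear scale.** With randomised arms and a 20-point difference in GTR, least squares gives

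total position effect = adjusted position coefficient + 0.20 × fitted GTR coefficient.

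The protocol gives no GTR-to-outcome effect, so the rows below are assumed scenarios. They were simulated with 2,000,000 patients each and GTR held at 93% and 73%. Outcomes are percentage points of good facial function, or minutes.

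| Assumption | Total | GTR-adjusted |
|---|---|---|
| No direct effect; GTR −20 points; no shared cause | −4.0 | 0.0 |
| Direct +10; GTR −20; no shared cause | +6.0 | +10.0 |
| No position or GTR effect; shared cause 0.10 per SD | 0.0 | −2.1 |
| Same, shared cause 0.15 per SD | 0.0 | −3.2 |
| No direct effect; GTR −20; shared cause 0.10 per SD | −4.0 | −2.1 |
| Direct +10; GTR −10; shared cause 0.10 per SD | +7.9 | +7.8 |
| Time: direct −30 min; GTR +30 min; no shared cause | −24 | −30 |
| Time: direct −30 min; GTR no effect; no shared cause | −30 | −30 |

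Check of row 3: the fitted GTR coefficient was 0.106, and 0 − 0.20 × 0.106 = −0.021. In row 5 the adjusted value (−2.1) is neither the total effect (−4.0) nor the direct effect (0). In row 6 the two shifts nearly cancel.

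**Size on the odds-ratio scale.** Logistic simulation, GTR again at 93% and 73%:

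- No position effect, shared cause acting on both GTR and facial function with log odds 1.0 per SD: true OR 1.00, adjusted about 0.85.
- Same with log odds 1.5 per SD: true OR 1.00, adjusted about 0.76 (0.73 to 0.78 as the baseline risk varies).
- No direct effect, GTR log OR −1, no shared cause: total 0.81 to 0.84, adjusted about 1.00.

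**Against sampling error.** 58 × 0.92 = 53 evaluable per arm. Assuming 70% good function, SE(log OR) = √[2 × (1/37.1 + 1/15.9)] = 0.42. The shifts are |ln 0.85| = 0.16 and |ln 0.76| = 0.27, or 0.4 to 0.65 SE. The chance of a false positive at nominal 5% would rise to roughly 7% to 10%.

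**The case against.** The strongest reply is that the protocol already plans a comparison by randomised group for each of the three outcomes, and these tests do not condition on resection. That stands. A reader might infer that following the plan leaves the trial with only a distorted answer on nerve function, or hides the cost of more complete resection altogether. The protocol does not support that, because the group tests would still carry the total effect.

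It can also be said that the models are additional: they follow the group tests, the ANOVA is described as "Association of the time of operation with SSP versus LP, tumour size, the percentage of gross total resection, and surgeons", and the Discussion cites a study that tied facial nerve preservation to extent of resection and not to position. Asking whether position matters at a given resection result is a legitimate question, so such a model need not be abandoned. But the regression is introduced as measuring the influence of position, the section covers primary and secondary outcomes, and the section on additional analyses {20b} only points back to it. Nothing marks these models as exploratory, or says which result governs if the two layers disagree.

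Two further readings go too far. With a direct log OR of +0.5, a GTR log OR of −1 and no shared cause, the total OR is about 1.35 and the adjusted OR about 1.66. That is not spurious bias: the model recovers the assumed direct effect, exp(0.5) = 1.65, which is a different estimand. Nor is the phrase about the percentage of GTR proof that a group figure would be used as a covariate. Table 3 defines the resection category for each patient, so this is loose wording.

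**Conclusion.** The point holds, within limits. In the facial, hearing and operating-time models the SSP v LP term is conditioned on an outcome that the protocol itself expects position to change. It does not estimate the total randomised effect, and it is a clean direct effect only if resection and outcome share no cause beyond tumour size and surgeon.

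The flaw is confined to the regression and ANOVA for these secondary outcomes. Neither the size nor the sign of the distortion can be derived from the documents. The shift from 1.00 to about 0.85 to 0.76 depends entirely on the assumed shared-cause strength of 1.0 to 1.5 log odds per SD. If resection alone carried the effect, a real total effect would appear as none; if resection is unrelated to the outcome, adjustment changes nothing. The grade is therefore should-fix, not must-fix.

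**What to change.** In {20a}, state that the adjusted SSP v LP effect on facial nerve function, hearing and operating time comes from models with position and baseline variables only: tumour size and surgeon, as already planned. The age stratum used in randomisation and, for the hearing model, baseline hearing may be added, but they are not needed to cure this problem.

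State that any model containing each patient's own resection category is reported separately as an exploratory association, and that its position coefficient is not read as the treatment effect. Say also that the comparisons without GTR govern if the results differ.

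The cost is a few sentences, best written before the data are analysed. Sample size, data collection and the primary analysis do not change, and the link between resection and nerve function can still be reported.

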### Objectives {7}

The objectives of this study are to compare the effects of different surgical positions (SSP and LP) on the outcomes of large VS, primarily including effectiveness and safety.

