**Withdrawal criteria**	
Patient wishing to interrupt participation in the study before the end	
Patient has a patent foramen ovale^a,b^	
Postoperative pathological diagnosis is non-schwannoma	

*VS* Vestibular schwannoma

^a^Screening method for the preoperative detection of a patent foramen ovale (PFO) for patients with planned SSP is transoesophageal echocardiography (TEE)

^b^If the patient has a PFO, he or she will not be excluded from the study, but the surgical position originally assigned will be changed to LP

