**Secondary outcomes**		
Facial nerve function	As one of the inclusion criteria, facial nerve function was documented photographically at rest and while performing standardized facial expressions at defined time points (preoperatively, discharge, and 6 and 12 months after surgery).	This feature was evaluated by two experienced neurologists and classified according to the HB grading system [29].
Hearing function	Hearing level will be analysed and evaluated using pure-tone audiometry (PTA) and speech discrimination score (SDS) according to the guidelines of the American Association of Otolaryngology–Head and Neck Surgery (AAO-HNS) classification [30].	Serviceable hearing was defined as either class A (PTA ≤ 30 dB, SDS ≥ 70%) or class B (30 < PTA ≤ 50 dB, SDS ≥ 50%) and non-serviceable hearing as class C (PTA > 50 dB, SDS ≥ 50%) or class D (any PTA, SDS < 50%).
Surgical positioning time		
Time of operation	Craniotomy time	
	Intradural microsurgery time	
	Scalp closure surgery time	
Hospital stay		
Total hospitalization fee		
General complications	Intracranial haematoma: head imaging examination will be performed within 3 h after surgery.	
	Cerebrospinal fluid leakage (incision leakage or nasal leakage).	
	Intracranial infection: postoperative fever, cerebrospinal fluid routine, and biochemical evidence of infection.	
	Cranial nerve disorders in the posterior group: drinking water choking cough, articulation disorder, etc.	
	Others	
Special complications	VAE	
	Others	
Recurrence		

*HB* House-Brackmann, *VAE* Venous air embolism

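### Patients with a patent foramen ovale operated on in the lateral position count as semi-sitting for every outcome, which dilutes harms specific to the semi-sitting position

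*Protocol article*

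**What the plan says.** Three parts of the protocol article fix how PFO patients are handled.

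- **Who is screened.** Footnote a to Table 2 reads: "Screening method for the preoperative detection of a patent foramen ovale (PFO) for patients with planned SSP is transoesophageal echocardiography (TEE"). Screening is described for planned SSP only.
- **What happens to them.** Footnote b keeps a patient with a PFO in the study, but "the surgical position originally assigned will be changed to LP". The body of the same table nevertheless lists "Patient has a patent foramen ovale" among the withdrawal criteria.
- **How they are analysed.** Section {20a} says they are "analysed according to the SSP group they were originally assigned after the LP surgery". This is the last sentence of the paragraph that assigns a test to each outcome. That paragraph includes "general complications, and special complications between the SSP and LP groups will be evaluated using Fisher’s exact test or chi-squared test", and it also covers surgical positioning time. Section {20b} adds no further analysis and refers back to {20a}.

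Safety is part of the stated aim: the Objectives section describes the outcomes as "primarily including effectiveness and safety". The Background says of SSP that "this position carries some potential risks, such as venous air embolism (VAE"), and goes on to name tension pneumocephalus and peripheral nerve injury. In Table 3, VAE is the only event named under "Special complications".

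**The concern.** For gross total resection, analysis by allocated group is the right default. The difficulty is that the article states no other rule for harms that come from the position itself. An SSP-allocated patient moved to LP does not face the risks of SSP surgery but still counts in the SSP denominator. Screening is tied to planned SSP, so these crossovers run only from SSP to LP. For any harm that is more frequent in SSP, the dilution therefore has a known direction: it favours the experimental arm, and recruiting more patients would not remove it.

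Surgical positioning time is mixed in the same way, because it depends on the position in which the patient is actually placed. A reader who wants the VAE risk of an operation done in SSP could not get it from the comparison as planned.

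**Working it through.** **Plan's own figure.** There is none to reproduce on this point. The article gives no PFO prevalence, VAE rate or positioning time. The only figures used from it are 58 patients per group and 8% shedding (Sample size {14}), which leave 58 × 0.92 = 53.4, or about 53 per group.

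**Formula.** Let f be the share of the SSP arm with a detected PFO, r_S the event risk when operated on in SSP, and r_L the risk in LP. Assume that risks are otherwise alike in patients with and without a PFO.

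- SSP group as randomised: (1 − f) × r_S + f × r_L
- LP group as randomised: r_L
- Difference: (1 − f) × (r_S − r_L)

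The difference keeps its sign and shrinks by the fraction f. The same algebra holds for mean positioning time.

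**Illustration.** All values of f and all event rates are assumed.

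| f | SSP group shows, r_S = 20%, r_L = 0% | Expected events in 58 | SSP group shows, r_S = 20%, r_L = 5% |
|---|---|---|---|
| 0 | 20% | 58 × 0.20 = 11.6 | 20% |
| 10% | 0.9 × 20% = 18% | 58 × 0.18 = 10.4 | 18% + 0.5% = 18.5% |
| 25% | 0.75 × 20% = 15% | 58 × 0.15 = 8.7 | 15% + 1.25% = 16.25% |
| 30% | 0.7 × 20% = 14% | 58 × 0.14 = 8.1 | 14% + 1.5% = 15.5% |

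In the last column the LP rate is 5%, so the difference falls from 15 points to 13.5, 11.25 and 10.5 points. That is again 90%, 75% and 70% of the undiluted difference. The reported SSP rate itself falls by exactly f only when r_L is zero.

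**Effect on the planned test.** Two-sided Fisher power at the 5% level with 53 per group, r_L = 0%:

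| r_S | f = 0 | f = 10% | f = 25% | f = 30% |
|---|---|---|---|---|
| 20% | 97% | 93% | 83% | 77% |
| 10% | 44% | 34% | 21% | 16% |

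The f = 0 column describes a trial without crossovers. It is not the power of an as-operated comparison, which would have fewer SSP patients.

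**Where the direction is not fixed.** If r_S = r_L, the rule changes nothing. If r_S < r_L, it makes SSP look worse than it is. The general complications named in Table 3 are haematoma, cerebrospinal fluid leakage, intracranial infection and lower cranial nerve disorders. The article states no SSP excess for any of them. Its Background lists less bleeding as a possible advantage of SSP, and its Discussion cites a comparison that found no difference in complication rates.

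**What an as-operated table would contain.** Only SSP-allocated patients are screened, so randomisation implies about the same undetected share f in the LP arm. Moving detected PFO patients into LP gives a PFO share there of 2f / (1 + f): 0.2 / 1.1 = 18% at f = 10%, and 0.6 / 1.3 = 46% at f = 30%. In the SSP-operated group it would be about zero.

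**The case against.** The strongest reply is that the as-randomised rule is not an error. Under Table 2, screening and a possible change of position are part of being allocated to SSP. The as-randomised comparison correctly estimates the harm and positioning time of that strategy and is protected by randomisation. Harm per operation done in SSP is a different question, and both questions are legitimate. This stands, and it is why the as-operated analysis should sit beside the as-randomised one and not replace it.

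A second reply is that a safety set by treatment received is often left to the statistical analysis plan, which is not shown. That would answer a complaint about silence. Here, however, the article fixes the PFO handling expressly, exempts no outcome, and says under {20b} that {20a} already covers additional analyses. It does not forbid a further table, but it plans none.

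A third reply concerns size. Both f and the VAE rate are assumed, and in the 20% v 0% example the loss is 1.2 events in 58 at f = 10% and 3.5 at f = 30%. This also stands: the direction for SSP-specific harms is firm, but the amount is not.

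A reader might infer that the rule makes SSP look safer on every complication. The documents do not support that, because understatement needs a higher risk in SSP and none is stated for the general complications.

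**Conclusion.** The point holds for VAE and for other harms more frequent in SSP, such as the tension pneumocephalus and peripheral nerve injury named in the Background. For these, the planned comparison shows (1 − f) of the difference by position used: 90% of it at f = 10% and 70% at f = 30%. Positioning time is diluted in the same proportion. This rests on risks (or times) being otherwise alike in patients with and without a PFO, and on an f that the article does not give.

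Two stronger inferences should be resisted. The as-randomised rule is not wrong for gross total resection, functional outcomes or the general complication comparison. Nor do the documents require the as-operated analysis to be the main safety analysis.

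Separately, Table 2 contradicts itself: PFO is a withdrawal criterion in the body, while footnote b and section {20a} keep the patient in. If the withdrawal entry were followed, these patients would leave the SSP denominator and the dilution would not arise, but the arms would differ in PFO status. The point is therefore fully settled only once those passages agree.

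**What to change.** - Keep the as-randomised rule in {20a} for gross total resection, facial nerve and hearing function, and the general complication comparison.
- Pre-specify, beside the as-randomised results, an analysis by position actually used for VAE and other SSP-specific complications (listed by name) and for surgical positioning time.
- Report the PFO crossovers as a separate row, with their number and their events, so that f is visible.
- Reconcile the withdrawal entry for PFO in Table 2 with footnote b and with {20a}.

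The cost is a few sentences and one extra table. The primary test and the sample size do not change. The drawback is that the as-operated comparison is not protected by randomisation, because detected PFO patients move only into LP. Showing both tables makes that imbalance visible but does not remove it, so the as-operated table should be read together with the as-randomised one.
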